In chronic pain rehabilitation, it is essential to address the factors mentioned above (McCracken, 2005). In this sense, the biomedical approach to education may promote the fear-avoidance model (Louw et al., 2011), while the pain neuroscience education (PNE) promotes patients’ understanding of chronic pain and changes maladaptive thoughts and cognitions (Moseley, 2002; Meeus et al., 2010) with a biopsychosocial approach limiting the fear-avoidance model (Louw et al., 2016b). PNE has shown positive results on the kinesiophobia, catastrophizing, pain intensity, disability, and physical performance in patients with CLBP (Moseley, Nicholas & Hodges, 2004; Ryan et al., 2010; Louw et al., 2011; Malfliet et al., 2017; Rufa, Beissner & Dolphin, 2018; Núñez Cortés et al., 2023a; Nuñez Cortés et al., 2023b). A recent meta-analysis has shown that the in-group PNE had better results than individual PNE for kinesiophobia (Romm et al., 2021), and it has been identified, in other types of health education, that there are greater benefits in those people who received the in-group intervention (Riemsma, Taal & Rasker, 2003), probably supported by the fact that educational sessions conducted in-group modality can facilitate learning through social observation of positive behaviors exhibited by other members within the group (Romm et al., 2021; Salazar-Méndez et al., 2024). However, there are no primary studies comparing the two PNE modalities directly. On the other hand, despite increasing evidence that SDH are influential factors in clinical health outcomes to a greater extent than the quality and availability of medical care (Daniel, Bornstein & Kane, 2018), there are no studies that analyze specifically the influence of SDH factors (*e.g.*, educational level) on the effectiveness of PNE (Salazar-Méndez et al., 2024).

We hypothesize that there will be significant differences in favor of the intervention in-group modality compared to the individual modality. Furthermore, the effects will be influenced by the social determinants of health in both experimental groups.

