### Study objectives

The objectives of this trial are: (1) to compare the clinical and psychosocial effectiveness of in-group modality and individual modality of pain neuroscience education (PNE) in patients with CLBP; (2) To analyze the influence of social determinants of health on post-treatment results.

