### Outcomes measures

#### Demographic information

Patients will self-report a variety of demographic and descriptive information *via* paper forms, including age, sex, comorbidities, medications commonly used, duration of symptoms, marital status, employed status, educational level, and economic income. Weight and height will be measured at the beginning of the assessments.

The social determinants will be categorized as follows: (I) employment status: employed *versus* unemployed; (II) educational level: participants will assigned to the lower educational level if they had not completed secondary education and to the higher educational level if they had completed secondary education or university studies (Núñez Cortés et al., 2023a; Nuñez Cortés et al., 2023b); (III) economic income will be categorized according to individual monthly taxable income. The cut-off point will be set at a value equal to or less than USD 545, which determines the degree of coverage provided by the Chilean public health system.

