### Data analysis

#### Statistical approach

The analysis of the data will be blinded, as each subject and condition will be coded by a consultant who will not be involved in the investigation. SPSS software version 25.0 will be used for all analyzes (SPSS Inc. Armonk, NY, USA). Data will be reported as mean with SD or median with interquartile range. Statistical analyzes were performed on an intention-to-treat basis, with imputation of missing data using the average of the remaining participants.

Normality tests will be performed using the Shapiro–Wilk test given the number of subjects needed for each group. In addition, the homogeneity of variance and the sphericity of the data will be determined. In the case of not assuming any of these assumptions, the Green-Hausser correction will be used for the interpretation of subsequent analyzes. A three-way repeated measures ANOVA will be conducted to analyze both primary and secondary outcomes. The factors considered in this analysis will include time and intervention. Additionally, the third factor will encompass variables such as employment status, education level, or income. In case of significant interaction, a two-way repeated measures ANOVA (time (pre-post) × intervention (in-group PNE, individually PNE, no intervention)) will be performed for each employment status (employed or unemployed). Furthermore, a two-way repeated measures ANOVA (time (pre-post) × intervention (in-group PNE, individually PNE, no intervention)) will be performed for each educational level (high or low). Lastly, a two-way repeated measures ANOVA (time (pre-post) × intervention (in-group PNE, individually PNE, no intervention)) will be performed for income (≤USD 545, or >USD 545). If interactions are detected in any of the 2-way ANOVAs, a *post-hoc* analysis will be conducted using multiple pairwise comparisons employing a *t*-test corrected by Bonferroni. The significance level will be set at 5%.

A stepwise multiple linear regression will be performed to estimate the influence of changes in primary and secondary outcomes. In each model, adjustments will be made for employment status, educational level, and income. In this analysis, the aforementioned variables will be sequentially incorporated into each model.

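### The regression on social determinants is called stepwise and names no arm, baseline or arm × determinant term, so by itself it cannot separate prognosis from modification of the PNE effect

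*Protocol article*

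**What the plan says.** Study objectives gives the second objective as "To analyze the influence of social determinants of health on post-treatment results". The Introduction's hypothesis is more specific: "the effects will be influenced by the social determinants of health in both experimental groups".

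Statistical approach contains two analyses that involve the determinants.

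- **Three-way repeated measures ANOVA.** Two of its factors are time and arm. A determinant is the remaining one: "Additionally, the third factor will encompass variables such as employment status, education level, or income". If the interaction is significant, time × intervention ANOVAs follow within each level of employment, education and income.
- **Regression.** Its purpose is given as follows: "A stepwise multiple linear regression will be performed to estimate the influence of changes in primary and secondary outcomes". The only terms that the text then lists are the three determinants, and it calls them adjustments. The entry rule is that "the aforementioned variables will be sequentially incorporated into each model".

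For the regression, the text names no arm term, arm × determinant term, baseline score, or p-value threshold for entry or removal. It is also unclear whether change in the outcome is the response or a predictor. Neither analysis is named as the one that answers Objective 2.

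**The concern.** The hypothesis is about effect modification: whether PNE works better or worse according to employment, education or income. The Discussion draws the same line when it notes that an earlier study linked education to expectation of recovery but not to the effectiveness of the education itself. A regression on the three determinants alone, pooled over arms, answers a different question, namely who changes more whatever the treatment. A purely prognostic determinant could then be reported as influencing the effect of PNE, and a real modifier could be diluted or cancelled.

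The second problem is the word stepwise. Its ordinary meaning is entry and removal by p-value, which inflates the coefficients that survive and makes their p-values too small. The sentence on sequential incorporation can be read as forced entry of all three, which does neither. An analyst could defend either procedure from the text, and the results would differ.

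**Working it through.** The plan states no figure for the regression, so there is none to reproduce. The numbers below illustrate size under assumptions.

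**Inputs.** Allocation is 1:1:1 (Abstract). The article gives three different totals: 20 per group = 60 (Sample size), 69 (Abstract), and 33 per arm = 99 (Abstract). All three are shown. Assumed: three binary determinants, each with 50% prevalence and latent correlation 0.3; residual SD 1; stepwise entry at p < 0.05 and removal at p ≥ 0.10; 2,000 simulated trials per setting.

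**1. What the pooled coefficient measures.** With equal arms, the coefficient without arm terms averages the arm-specific determinant effects.

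- Modifier δ in both PNE arms, none in control: (0 + δ + δ)/3 = 2δ/3. For δ = 0.8 SD this is 0.53 SD; simulation gives 0.525 to 0.534. A prognostic effect of 0.53 SD in every arm gives the same coefficient.
- Opposite modifiers in the two PNE arms: (0 + 0.8 − 0.8)/3 = 0. The determinant is significant in about 4% of trials. An arm × determinant F test detects the pattern in 56%, 59% and 80% of trials at N = 60, 69 and 99.

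**2. What stepwise selection does, if that is what is meant.** One determinant has a true effect and the other two have none.

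| N | True effect (SD) | Kept | Mean when kept (SD) | Mean, all three forced in (SD) | 95% CI coverage, forced |
|---|---|---|---|---|---|
| 60 | 0.3 | 20% | 0.66 | 0.31 | 95% |
| 69 | 0.3 | 23% | 0.63 | 0.31 | 95% |
| 99 | 0.3 | 32% | 0.53 | 0.30 | 95% |
| 60 | 0.5 | 45% | 0.72 | 0.49 | 95% |
| 69 | 0.5 | 52% | 0.68 | 0.50 | 95% |
| 99 | 0.5 | 68% | 0.61 | 0.50 | 96% |

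The inflation runs from 0.607/0.5 = 1.21 to 0.658/0.3 = 2.19, that is, about 20% to 120%. At N = 69 with a true 0.3 SD, the 95% interval of a kept coefficient covers the truth in 85% of trials. With a true 0.5 SD, coverage is close to nominal (93% to 96%), so the damage is greatest for small effects.

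**3. How wide an interaction interval would be.** With n per arm, a 50:50 determinant and residual SD 1, the variance of the determinant effect in one arm is 1/(n/2) + 1/(n/2) = 4/n. For the difference between two arms it is 8/n. The 95% half-width is 1.96 × √(8/n):

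- n = 20: 1.24 SD
- n = 23: 1.16 SD
- n = 33: 0.97 SD

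In line with this, a modifier of 0.8 SD in both PNE arms is detected by the interaction F test in only 21%, 24% and 34% of trials at N = 60, 69 and 99.

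**The case against.** The strongest answer is that effect modification is already tested. The three-way ANOVA includes time, intervention and a determinant, so time × intervention × determinant is available, with follow-up analyses by level. This stands. A reader might infer from the regression that the plan cannot answer Objective 2; the documents do not support that. Objective 2 as worded is also loose enough for a main-effect regression to address part of it, and a prognostic regression beside an interaction ANOVA is not in itself an error. What remains is that the ANOVA takes the determinants one at a time, the regression is the only step that considers all three together, and no rule says which governs if they disagree.

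A reader might also take it as settled that predictors are chosen by p-value. That is the plain reading of stepwise, but no threshold is given, and adjusting for all three in sequence fits forced entry. On that reading the inflation disappears.

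The arm is unlisted rather than expressly excluded. Calling the determinants adjustments suggests some other main predictor, and the article lists a full trial protocol as a supplement that is not shown. This limits the point to the published wording.

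Two further inferences should not be pressed.

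- **False entry.** The chance that at least one of three null determinants is kept reflects ordinary multiplicity (1 − 0.95³ = 14.3% for independent tests). Entering all three together and testing each at 5% does not remove it, so it is no evidence against stepwise selection.
- **Employment and income.** These may overlap, since "economic income will be categorized according to individual monthly taxable income". A correlation of 0.34 to 0.73 follows only if one assumes 50–80% employed, 40–70% of those above the USD 545 cut-off, and no unemployed participant above it. The article gives no such data, so overlap is a possibility to check.

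**Conclusion.** The point holds in limited form. As published, the regression estimates determinant associations pooled over arms and cannot by itself support a statement that determinants influence the effect of PNE. The dilution to 2δ/3 follows from equal allocation alone. The cancellation example assumes opposite effects in the two PNE arms.

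The inflation of kept coefficients, about 20% to 120% for true effects of 0.3 to 0.5 SD, depends on p-value selection and on the simulation's assumed prevalences, correlation and thresholds. Under forced entry it is absent, and the label is then simply wrong. Either way the entry method needs one clear statement.

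Objective 2 is not unaddressed, because the three-way ANOVA serves it; the gap is that the plan does not say which analysis carries the conclusion. The primary comparison of arms is unaffected. The revision is worth making before analysis because it concerns one of the trial's two stated objectives.

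**What to change.** 1. Delete the word stepwise and the sequential-entry sentence.
2. For each outcome, pre-specify one linear model of follow-up score on baseline score, arm, and all three determinants entered together.
3. Add arm × determinant terms for one determinant at a time, keeping all main effects. Report the interaction estimates with 95% confidence intervals, labelled exploratory.
4. State that the interaction, in this model or in the three-way ANOVA, is the basis for any claim that a determinant influences the effect of PNE, and say which of the two takes precedence. Describe determinant main effects as prognostic.
5. Cross-tabulate employment by income. If few or no unemployed participants are above the cut-off, interpret the two jointly.

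The cost is analysis wording only, with no new data. The downside is wide interaction intervals, roughly ±1.0 to ±1.2 SD under the assumptions above, so conclusions on Objective 2 will have to be modest.

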#### Sample size

Sample size calculation was performed with G*Power 3.1. A repeated measures analysis of variance (ANOVA) model with within-between interaction, was used. Assuming an alpha risk of 0.05, a power of 0.95, a correlation between repeated measures of 0.5, a 10% drop-out rate, and a small effect size (0.26), a total of 20 participants per group (three groups) were required. The effect size estimate was based on a previous study about education compared to physical therapy for the FABQ outcome (Marshall et al., 2022) and the recommended effect size for clinical studies (Lakens, 2013).

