The calculation of Cohen’s d will be performed to determine the effect size (ES) of all intragroup variables. Consider a small effect size if it is less than or equal to 0.2; medium of 0.3 to 0.5 and large of 0.5 to 0.8 (Jacob, 1992).

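### The only effect size named is within-arm, although the trial's question is between arms, and its grading bands overlap at 0.5 and leave gaps

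*Protocol article*

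**What the plan says.** The last paragraph of the Statistical approach section (Protocol article, Data analysis) fixes the effect size as Cohen's d, to "determine the effect size (ES) of all intragroup variables". It then sets the labels: "Consider a small effect size if it is less than or equal to 0.2; medium of 0.3 to 0.5 and large of 0.5 to 0.8". No other effect size is named for reporting results.

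The question is a between-arm one. The Introduction predicts "significant differences in favor of the intervention in-group modality compared to the individual modality". Study objectives puts the comparison of the two modalities first, and the design adds a usual-care control.

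The same section describes the between-arm analysis as a repeated measures ANOVA: "The factors considered in this analysis will include time and intervention", with employment, education or income as a third factor. If there is a significant interaction, two-way ANOVAs follow within the levels of those social factors. If these in turn show an interaction, the plan goes on to "multiple pairwise comparisons employing a *t*-test corrected by Bonferroni". The section mentions no between-arm difference or confidence interval.

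**The concern.** A within-arm d measures how far an arm moved from its own baseline. It mixes the effect of the intervention with whatever would have moved the arm anyway, such as natural course and repeat testing. It cannot separate the two PNE modalities, or either of them from usual care.

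This design makes shared change plausible. The Intervention section says that both PNE arms receive the same content and differ only in delivery, to groups of 3–5 or to one person. Both arms may therefore show a sizeable d even if modality makes no difference. The d is calculated unconditionally, whereas the pairwise comparisons depend on earlier significant results. The magnitude that readers are sure to see is then the one that does not address the hypothesis.

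The labels add a second problem: some results would carry two labels and others none.

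**Working it through.** The plan computes no figure on this point that could be reproduced. The check has three parts.

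**1. The bands, read as written**

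- Small: d ≤ 0.2. Medium: 0.3 to 0.5. Large: 0.5 to 0.8.
- Overlap: the single value 0.5 is both medium and large.
- Gaps: 0.2 < d < 0.3 and d > 0.8 have no class.

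**2. What a within-arm d can show**

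Let every arm change by the same c (in SD units), with no added effect of either intervention. The within-arm d is c in each arm. The between-arm d is c − c = 0. Conversely, d = 0.5 in both PNE arms fits a shared change of 0.5 with no treatment effect, and equally no shared change with an effect of 0.5 against control. In both cases in-group minus individual is 0.

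**3. Size under sampling variation**

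Inputs:
- Pre-post correlation 0.5, from the Sample size section.
- Arm sizes of 33 (Abstract), 23 (69/3, from the Abstract total) and 20 (Sample size section). That these disagree is a separate matter.
- Identical change of 0.3 to 0.6 SD in all three arms. This is an assumption; the document gives no figure.

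Method: 20,000 simulated trials per setting. Within-arm d = mean change / √[(baseline variance + follow-up variance)/2]. Between-arm d = difference in mean change (PNE minus control) / pooled baseline SD.

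| n per arm | Common change (SD) | Mean within-arm d | Arm has d ≥ 0.3 | Arm has d ≥ 0.5 | 0.2 < d < 0.3 | d > 0.8 | Mean between-arm d |
|---|---|---|---|---|---|---|---|
| 33 | 0.3 | 0.30 | 51% | 14% | 21.2% | 0.5% | 0.00 |
| 33 | 0.4 | 0.41 | 71% | 30% | 16.1% | 1.7% | 0.00 |
| 33 | 0.5 | 0.51 | 87% | 51% | 8.3% | 6.1% | 0.00 |
| 33 | 0.6 | 0.61 | 96% | 72% | 3.3% | 15.4% | 0.00 |
| 23 | 0.5 | 0.51 | 83% | 51% | 9.4% | 9.9% | 0.00 |
| 20 | 0.5 | 0.51 | 81% | 51% | 9.9% | 11.8% | 0.00 |

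Adding the two gap columns for 33 per arm, the share of arm results with no label is 21.2 + 0.5 = 21.7% at 0.3 SD, 16.1 + 1.7 = 17.8% at 0.4, 8.3 + 6.1 = 14.4% at 0.5, and 3.3 + 15.4 = 18.7% at 0.6.

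**Precision.** With correlation 0.5 the variance of change is 2(1 − 0.5) = 1 SD². Ignoring error in the estimated SD, the approximate 95% half-widths are:

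- Within-arm, 1.96·√(1/n): 0.34 (n = 33), 0.41 (n = 23), 0.44 (n = 20).
- Between-arm, 1.96·√(2/n): 0.48, 0.58, 0.62.

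The between-arm interval is wider by a factor of √2, so a within-arm d also looks more precise than the contrast the trial is about.

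**The case against.** The strongest reply is that the treatment question is tested between arms. The ANOVA includes intervention as a factor with the control as one of its levels, and a change shared by all arms produces no time-by-intervention interaction beyond the 5% error rate. The d is not restricted to the PNE arms, so the control arm would be graded too, and an equal d there would reveal that the change is shared. This stands. A reader might infer that common change will be reported as a medium or large treatment effect. The document does not support that, because nowhere does it say that the within-arm d will be read as the treatment effect. The risk is one of misreading.

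It can also be said that confidence intervals and the choice of standardiser are reporting detail that an article leaves to the full protocol, and that the planned means and SDs let a reader derive differences. In part this holds. But the article does not stay silent on effect size: it names one, and that one does not match its hypothesis. Means and SDs at each time give a raw difference in change, but not its confidence interval without the pre-post correlation.

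Three further inferences are tempting and not supported:

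- That the planning effect of 0.26, called small in the Sample size section, falls into the plan's own gap. It was entered in G*Power for a repeated measures ANOVA and is probably Cohen's f. The metric is not named, and an f cannot be placed on bands for d.
- That regression to the mean will inflate the primary outcome. The entry window concerns pain intensity, is two-sided (3 to 8), and applies to a secondary outcome. FABQ is not an entry criterion.
- That the bands raise results by one class compared with the source they cite. That source is not at hand.

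**Conclusion.** The concern holds in a limited form. The only effect size the plan names describes change within an arm, so it cannot quantify the contrast in the objective and hypothesis. The grading rule gives two labels at one value and none over two ranges. Both defects are visible in the text and need no assumption.

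The illustration of size does rest on assumptions: a common change of 0.3 to 0.6 SD, correlation 0.5 and normal data. At 0.5 SD with 33 per arm, a given arm reaches d ≥ 0.3 in 87% of trials and d ≥ 0.5 in 51%, with a between-arm d averaging zero. Across the range run with 33 per arm, about 14% to 22% of arm results would have no label.

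No hypothesis test or sample size depends on this, and the between-arm test remains in place. It is worth correcting because following the rule as written yields magnitudes that do not answer the trial's question.

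**What to change.** In the effect-size paragraph of Statistical approach:

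- Report, for each outcome and follow-up time, the between-arm difference in change with its 95% CI for in-group against individual PNE and for each against control, whether or not an interaction is significant.
- Add a between-arm standardised difference for the same contrasts and name the standardiser, for example the pooled baseline SD.
- Read FABQ differences against the MCIDs given under Primary outcomes: 4 points for the physical activity scale and 7 for the work scale.
- Keep the within-arm d as descriptive, shown for all three arms together.
- Either drop the labels, or define contiguous bands so that every value has exactly one class and the top band is open-ended, after checking them against the cited source.

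The cost is analysis wording and slightly more analysis work, with no new data. The between-arm effects will probably look smaller and less precise than the within-arm d.

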## Discussion

CLBP is considered to be one of the most prevalent health conditions, contributing significantly to the global burden of disease (Rabiei, Sheikhi & Letafatkar, 2021). Therefore, it is relevant to determine cost-effective therapeutic strategies that can improve the clinical condition of patients. In this sense, therapeutic strategies directed by physical therapists based on the biopsychosocial (BPS) model have been shown to effectively improve symptoms in people with spinal disorders (Miki et al., 2023).

PNE is based on the BPS model (Nijs et al., 2011; Moseley & Butler, 2015) and has been shown a to have positive effect on pain, disability, catastrophism, kinesiophobia, physical performance, and a reduction in health care costs in subjects operated for radiculopathy (Louw et al., 2011; Louw et al., 2016a; Gallagher, McAuley & Moseley, 2013; Mittinty et al., 2018). This may be because it influences pain cognitions, an important aspect in the vicious circle of central sensitization in patients with CLBP even when not all present with such sensitization (Huysmans et al., 2018). However, PNE implemented in isolation may not generate significant clinical effects (Louw et al., 2016c; Louw, Puentedura & Zimney, 2016; Puentedura & Flynn, 2016). While PNE performed in a group modality could potentially facilitate learning through social observation, which would provide a positive influence on therapy due to the observation of the behaviors exhibited by other participants (Romm et al., 2021).

The lack of effectiveness of the PNE applied in isolation may be because it has been approached mainly from the neurophysiology of chronic pain with little orientation of the contents to the context of the person. Furthermore, a very small number of studies have considered within the demographic characteristics the educational level of the subjects (Malfliet et al., 2017; Mittinty et al., 2018; Rufa, Beissner & Dolphin, 2018); and of these, only one used this data to be analyzed, however, it was used as a secondary variable and it was evidenced that a high educational level is associated with the expectation of recovery, not with the very effectiveness of the intervention of education (Mittinty et al., 2018), In addition, these studies tended to present more subjects with high educational levels, however, it has been shown that people who are more predisposed to have lumbar pain chronification have a low level of education (Meucci et al., 2013).

It follows that the studies have not considered in their analysis the possible differences in the effectiveness that may exist in the application of pain neuroscience education with orientation to the context according to the educational level and other SDH related to the socioeconomic level of the subjects to whom this intervention is applied, evidencing a knowledge gap since this could influence the effects of this type of educational therapy.

This study will provide new data on the efficacy of pain neuroscience education focused on fear-avoidance beliefs on clinical and psychosocial variables in patients with CLBP, differentiating the effects between in-group and individual approaches and the influences of social determinants of health. This will allow the identification of strategies for the implementation of PNE in clinical contexts that allow a better cost-effectiveness of the intervention.

